# Effectiveness of therapeutic ultrasound for the treatment of carpal tunnel syndrome (the USTINCTS trial): study protocol for a three-arm, prospective, multicentre, randomised controlled trial

**DOI:** 10.1136/bmjopen-2021-057541

**Published:** 2022-04-13

**Keywords:** REHABILITATION MEDICINE, SPORTS MEDICINE, Hand & wrist, Orthopaedic sports trauma

## Abstract

**Introduction:**

There has no consensus on optimal management of carpal tunnel syndrome (CTS), the most common compression neuropathy. Conservative therapy is generally accepted as first-line intervention. Therapeutic ultrasound has been widely reported to be treatment beneficial in nerve regeneration and conduction, and further accelerate compression recovery. The purpose of this study is to investigate the effectiveness of therapeutic ultrasound for CTS treatment.

**Methods and analysis:**

This study protocol entails a three-arm, prospective, multicentre, randomised controlled trial. 162 eligible adult participants diagnosed with mild to moderate CTS by using criteria developed from a consensus survey by the UK Primary Care Rheumatology Society will be assigned to either (1) therapeutic ultrasound, (2) night splint or (3) therapeutic ultrasound +night splint (combined) group. Primary outcome will be difference in Symptom Severity Scale of Boston Carpal Tunnel Questionnaire (BCTQ-SSS) at 6-week between night splint and therapeutic ultrasound +night splint groups. Secondary outcomes include Functional Status Scale of BCTQ, sleep questionnaire for interrupted sleep, EuroQol-5D for general health, Hospital Anxiety and Depression Scale for mental status, Work Limitations Questionnaire-25 for functional limitations at work, Global Rating of Change for treatment success and recurrence rate, physical examination, electrophysiological and ultrasound parameters. Intention-to-treat analyses will be used.

**Ethics and dissemination:**

Ethics committees of all clinical centres have approved this study. The leading centre is Shanghai Sixth People’s Hospital, whose approval number is 2021-152. New versions with appropriate amendments will be submitted to the committee for further approval. Final results will be published in peer-reviewed journals and presented at local, national and international conferences.

**Trial registration number:**

ChiCTR2100050701.

Strengths and limitations of this studyTherapeutic ultrasound as independent or adjunct therapy in treating carpal tunnel syndrome (CTS).The first randomised controlled trial (RCT) to compared the efficacy between therapeutic ultrasound and night splint in CTS treatment.Multicentre RCT with blinded outcome assessor and statistician.Use of several patient-reported outcome measures as well as objective parameters.Participants and treating surgeons not blinded.

## Introduction

Carpal tunnel syndrome (CTS), the most common compression neuropathy, results from median nerve entrapment in the carpal tunnel, accounting for about 90% of all such disorders.^1 2^ The clinically confirmed CTS prevalence was 9.6% in the general population of China,^3^ with a yearly incidence rate of 2.76‰, and women is more susceptible than men.^2 4^ CTS has significant impact on daily life and ability to work,^5^ and causes great burden on social economy, with an annual associated costs estimated at US$13 billion.^6^ Classically, CTS causes discomfort, paraesthesia and numbness in the median nerve distribution; and nocturnal symptoms are often clinically significant causing sleep disturbance.^7^ Patients can be diagnosed by clinical history and physical examination; while electrophysiological methods will be additional for insufficient diagnosis by clinical findings and severe cases that need surgical management.^8^

In general, the severity of CTS can be classified into mild, moderate and severe.^9^ Non-surgical interventions are suggested to be the first choice to treat mild and moderate CTS.^10^ To date, though the treatment method is vast; however, no successful and universally accepted regimen has been established. A consensus of multidisciplinary treatment guideline from the European HANDGUIDE Study suggests that ‘education’ should be included as the first-line management approach, which has the advantages of low cost, high efficacy and non-invasiveness.^7 11^ In addition, ‘night splint’ and ‘corticosteroid injection’ are also recommended in guidelines of American Academy of Orthopaedic Surgeons and American Physical Therapy Association.^12 13^ One recent randomised controlled trial (RCT) published in Lancet compares both two methods, and finds that corticosteroid injection has superior clinical effectiveness at 6 weeks than night splint, but no differences at 6 months; while corticosteroid injection may bring adverse events like thinning, lightening or darkening of the skin at the injection site, hot flushes and even more pain.^9^ Systematic reviews have also shown that the effects of other conservative treatments like acupuncture,^14^ exercise and mobilisation interventions,^15^ laser,^16^ extracorporeal shockwave therapy^17^ and platelet-rich plasma injection^18^ still remain controversial or provide little to no benefit.

Therapeutic ultrasound (US) is widely used for imaging purposes and regarded as an adjunct to physiotherapy. In the intensity range of 0.5–2.0 W/cm^2^, therapeutic US may have the potential to induce a variety of biophysical effects in tissues.^19^ Therapeutic US experiments on stimulation of nerve conduction and regeneration,^20 21^ and discoveries of its anti-inflammatory effects^22^ all support that therapeutic US may promote recovery of nerve compression. An RCT published in BMJ showed more pronounced subjective symptoms and electroneurographic variables for therapeutic US than sham control in patients with mild to moderate CTS.^23^ However, to our best of knowledge, no study has compared the efficacy between night splint and therapeutic US in CTS treatment yet. Additionally, some studies have also reported the efficacy of US to be used as part of a multi-intervention approach, but with low grade of study design and data.^24–29^ Therefore, the role of therapeutic US in CTS treatment still needs to be further explored by high-quality study.

Therefore, the purpose of the current three-arm, prospective, randomised, multicentre trial is to examine the effectiveness of therapeutic US in treatment for CTS, that is, night splint +therapeutic US (combined) vs night splint vs therapeutic US, on clinical and functional outcomes, including Boston Carpal Tunnel Questionnaire (BCTQ) in patients diagnosed with CTS.

## Methods

### Study design

This study is a three-arm, prospective, multicentre, RCT that will recruit participants from four municipal tertiary hospitals with a diagnosis of mild to moderate CTS. The multicentres are Shanghai Sixth People’s Hospital, Shanghai Tenth People’s Hospital, Shanghai East Hospital and Pudong New Area People′s Hospital of Shanghai, respectively. This manuscript is written according to the Standard Protocol Items: Recommendations for Interventional Trials (SPIRIT) guidelines.^30^

### Participant and public involvement

There was no participant involvement in this study. Participants were not invited to make comments or suggestions on the protocol, were not consulted about the selection of patient-relevant evaluation outcomes, or were invited to participate in writing or editing the manuscript to improve readability or accuracy. The final findings will be disseminated to the public through mass media. Our published papers and conference presentations also acknowledge all participants as a whole.

### Participant recruitment

Figure 1 shows the participant flow chart throughout the study. Participants will be recruited over a 5-month period from outpatient clinics of four principals in each subcentre. In addition, recruitment can also be through other doctors and healthcare professionals. Interested participants can contact the research assistant, who will provide more information about the study purpose and protocol, and conduct an initial eligibility screening by phone.

**Figure 1 F1:**
[figure not shown]
Participant flow chart.

### Medical evaluation and enrolment procedure

Eligible participants will be invited to participate in a physical examination to confirm CTS diagnosis and assess eligibility to participate in the programme.

#### Inclusion criteria

Age ≥18 years old.Clinical diagnosis on the basis of clinical symptoms, history and physical examination, using criteria developed from a consensus survey by the UK Primary Care Rheumatology Society.^31^Mild to moderate CTS,^9^ with symptoms longer than 6 weeks duration; participants with bilateral CTS will be designated their study hand based on the most severe symptoms.Mild: intermittent paraesthesia in the distribution of the median nerve.Moderate: constant paraesthesia, and reversible numbness or pain of idiopathic nature.Severe: constant pain, numbness or sensory loss in the wrist and hand (specifically palm, index, or middle finger, or thumb), or thenar muscle atrophy.Able to read and write in simplified Chinese (Mainland), understand and complete the questionnaire, and should provide informed consent.

#### Exclusion criteria

CTS secondary to wrist deformity, trauma, mass, pregnancy, hypothyroidism or inflammatory arthropathy.Treatment by night splint, therapeutic US or injection within the past 6 months or previous carpal tunnel surgery.Previous surgery on the affected wrist (or study wrist if bilateral CTS).Unable to tolerate the study interventions.Trauma to the affected upper limb requiring operation or immobilisation within the past 12 months.Current illness including, poorly controlled diabetes mellitus or thyroid disease, vibration-induced neuropathy, osteoarthritis or inflammatory joint disease, suspected complex neurological and musculoskeletal conditions.Known drugs or alcohol abuse.Allergy to any of the splint materials.Contraindications to therapeutic US, including dermatological conditions, abnormal sensation in the affected arm, indwelling electrical pumps/pacemakers, epilepsy, pregnancy or breast feeding.

Following the medical evaluation, a research assistant will meet with the eligible participants and obtain their written informed consent. Demographic variables such as age, sex, body mass index, affected wrist (whether bilateral), dominant arm, lifestyle (smoking and alcohol use) and medical history of all participants will be collected prior to treatment (baseline). Participants will also be asked relevant questions about symptoms duration and previous treatments (rehabilitation exercises, injections or others). Others like occupation, employment characteristics (full-time or part-time work, manual or non-manual labour), employment status (whether on sickness absence), and professional activity characteristics (repetitive movements for >4 hours/day; wrist flexion and extension for >2 hours/day and use of computer keyboard/mouse (how many hours/day)) will be also collected.

### Randomisation and blinding

Participants will be randomised in three intervention groups (either therapeutic US or night splint or therapeutic US+night splint arm) in a ratio of 1:1:1, using a computer-generated randomised sequence with varying unknown block sizes (either 3 or 6) for all study centres, without stratification. A research assistant who are not involved in clinical care and participant evaluations will prepare sequentially numbered, opaque, sealed envelopes based on a random list, and ensure that the allocation data will not be accessed or influenced by anyone. When appropriate, the assistant will open envelopes and ensure coordination of therapeutic interventions.

The outcome assessor and statistician will be blinded to group allocation and not involved in treatment procedures.

### Intervention

At the beginning, all participants will participate in an about 30 min group educational presentation by a research assistant on the same day as the baseline assessment. This presentation will cover the pathophysiology, treatment options, posture and activity modification principles of CTS. The above information will also be provided to participants in the form of education booklets, to encourage them to review at home. Habits changes include limited wrist movement and a reduction in strenuous work activities, and the use of ergonomically friendly work tools helps reduce median nerve pressure.^32 33^

Participants in the (therapeutic US group) will receive pulsed therapeutic US (model 1:4, Shanghai, China) for 6 weeks at a frequency of 1 MHz and intensity of 1.0 W/cm^2^ for 15 min per session, in daily five times a week for the first 2 weeks and twice a week for another 4 weeks, to the area over the carpal tunnel, referred to a published trial (BMJ. 1998;316:731–735).

Participants allocated to the (night splint group) will receive a splint to wear at night for 6 weeks, referred to a published trial (Lancet. 2018;392:1423–1433). The splint holds the wrist in a neutral position or slightly extended 20° from the neutral position to avoid wrist movement, which can increase pressure on the carpal tunnel.^34^ The choose of each splint will be based on the size of individual participant’s hands and arms. Participants will be shown how to fit and remove the wrist splint according to a standardised trial protocol. Oral guidance from the clinician on how and when to use splints will encourage and reinforce compliance, which will be also supported by written information, detailed care and splint fitting and use. Participants will be instructed to perform gentle range-of-motion exercises when removing the splint to prevent stiffness.

Participants randomised to the (therapeutic US+night splint group) will receive both therapeutic US for 6 weeks as in the (therapeutic US group) and night splint for 6 weeks as in the (night splint group).

For participants with bilateral CTS, the non-study hand will be treated according to normal clinical protocols in use at the research site.

We discouraged additional treatments to that assigned (ie, not per protocol) during the intervention period, but we allowed the use of simple analgesics as needed. Participants reported all not per protocol treatments, such as drugs, in a diary.

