### Primary outcome measure

The primary outcome measure will be the difference in Symptom Severity Scale of the Boston Carpal Tunnel Questionnaire (BCTQ-SSS) at 6 weeks. The BCTQ is a disease-specific questionnaire referring to a typical 24-hour period in the past 2 weeks,^35^ and has been shown to be highly reproducible, internally consistent, valid and responsive to clinical change in CTS.^36^ It consists of two different subscales: Symptom Severity Scale (11 items, about symptom severity) and Functional Status Scale (8 items, about the degrees of difficulty on daily activities), both rated on a five-point scale, with final scores for each subscale result in mean scores between 1 and 5. The overall score is calculated as the mean of all 19 items. Higher scores represent more severe symptoms and functional impairment. We use a validated Chinese version^37^ of the BCTQ in this study.

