Interrupted sleepThe sleep questionnaire, which will be used to assess sleep quality, consists of four questions asking participants how many times they have experienced it in the last month.^38^ Each question has six response categories and are coded in 0–5 order: not at all, 1–3, 4–7, 8–14, 15–21 and 22–31 days. All questions have equal weights and add up. Higher scores are associated with more disrupted sleep.Life quality and health statusEQ-5D has been widely validated and used to measure generic health-related quality of life (HRQol) due to its simplicity.^39^ It consists of a five-dimensional description system (mobility, self-care, usual activities, pain/discomfort and anxiety/depression) and a visual analogue scale that scales from 0 to 1, where 1 represents perfect health. All dimensions are divided into three levels (no problem, some problem and extreme problem). We used a validated Chinese version^42 43^ of EQ-5D, which has been recommended by Guidelines for Pharmacoeconomic Evaluations 2011 for a measure for HRQol and health utility.^44^Anxiety and depression statusHADS will be used to identify and quantify two of the most common psychological disorders - anxiety and depression.^40^ There is evidence of increased anxiety and depression in LET patients.^45^ The HADS is a 14-item scale independent of physical symptoms and consists of two 7-item subscales measuring depression and anxiety, respectively. A four-point scale (0 for absence of symptoms and 3 for maximum symptomatology) is used. Each subscale has an overall score ranging from 0 to 21, with a higher score indicating a higher degree of impairment. HADS has two cut offs for categorisation: 0–7, ‘non-case’; 8–10, ‘possible or doubtful case’; 11–21, ‘probable or definite case’.^46^Functional limitations at workTo gather information that is complementary to the pain and disability scales, functional limitations at work will be measured using WLQ-25. It contains 25 items, arranged under four subscales, covering four dimensions of job demands, namely time demands, physical demands, mental/interpersonal demands and output demands.^41^ A five-level ordinal response scale ranging from 0 (all of the time) to 4 (none of the time) with an additional sixth option (does not apply to my job) is used. The overall score ranges from 0 to 100, with an increase of 13 points (out of 100) for clinically important differences.^47^Treatment success and recurrence rateParticipants’ treatment impressions of changes in their condition (ranging from ‘completely recovered’, ‘much improved’, ‘somewhat improved’, ‘same’, ‘worse’ to ‘much worse’) will be recorded on a six-level Likert scale. The success rate will be calculated by dichotomising the response. Participants who report ‘completely recovered’ or ‘much improved’ in their overall condition since the study beginning will be considered successful, while other responses will be considered failures.^48 49^ Recurrence will be defined primarily as when a participant rates a success at 6 weeks and a failure at 3 months, 6 months or 1 year on GROC.^48 49^Physical function examinationThe physical examinations will include measurement of two-point discrimination (performed on the radial and ulnar aspects of each digit), grip strength with a dynamometer (CAMRY, City of Industry, California, USA), and pinch strength with the pinch gauge (three trials for each hand). The affected side will be measured first and then the unaffected side. The measurement readings will be not revealed to the subjects until the completion of the test. The mean of three consecutive trials, separated by a 20 s pause, will be calculated. Results will be presented as a ratio of values of the symptomatic side/asymptomatic side ×100.^50^The two-point discrimination test starts at a distance of 4 mm and increases continuously by 2 mm as necessary. Grip strength and three-point pinching force (three tests per hand) as measured with baseline dynamometer and pinch gauge (Chattanooga Group, Hixson, Tennessee, USA) will be recorded.Electrophysiological studyMedian nerve distal motor latency (DML), compound muscle action potential (CMAP), sensory nerve conduction velocity (SNCV) and sensory nerve action potential (SNAP) amplitudes will be recorded.^48 49^ DML and CMAP will be measured by placing surface electrodes on the abductor pollicis brevis muscle, and stimulation applied 8 cm proximal to the active recording electrode. SNAP and SNCV will be obtained using ring electrodes placed on the proximal and distal interphalangeal joints of the index finger. Sensory conduction will be studied by antidromically stimulation at 14 cm proximal to the active electrode. Motor study will be performed by supramaximal stimulation while the amplitude will be measured an average of 10 times for the sensory study. All measurements will be made three times, and the values obtained will be averaged for analysis.US parametersThe cross-sectional area will be measured using an electronic calliper at the scaphoid-pisiform level.^51 52^ The measurements will be made three times, and the values obtained will be averaged for analysis.

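### In bilateral participants, success and recurrence are rated on overall condition and not on the study hand, so the non-randomised hand can change both; the article does not say which hand the primary questionnaire rates.

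*Protocol article*

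**What the plan says.** The Inclusion criteria of the Protocol article admit bilateral disease and name one hand for study: "participants with bilateral CTS will be designated their study hand based on the most severe symptoms". The Intervention section leaves the remaining hand to the centre: "For participants with bilateral CTS, the non-study hand will be treated according to normal clinical protocols in use at the research site". That section also says "We discouraged additional treatments to that assigned (ie, not per protocol) during the intervention period" and has participants record off-protocol treatment in a diary. It does not say whether routine care of the non-study hand counts as off-protocol and belongs in the diary.

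In the Secondary outcome section, treatment success comes from a six-level global rating. Participants choosing one of the top two categories "in their overall condition since the study beginning will be considered successful, while other responses will be considered failures". Recurrence is a success at 6 weeks followed by a failure on the same rating at 3 months, 6 months or 1 year.

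For the primary outcome, "The primary outcome measure will be the difference in Symptom Severity Scale of the Boston Carpal Tunnel Questionnaire (BCTQ-SSS) at 6 weeks", the article gives scoring and a time frame, "The BCTQ is a disease-specific questionnaire referring to a typical 24-hour period in the past 2 weeks". It names no hand.

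Bilateral status is among the baseline data collected before treatment. The Analysis plan does not mention it, although its list of covariates is left open.

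**The concern.** Randomised treatment is given to one hand, but success is scored on the whole person. For a unilateral participant the two nearly coincide. For a bilateral participant they need not, because a second diseased hand is managed by rules that the trial does not set and that may differ among the four centres.

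Two things are at stake. The first is dilution: ratings driven by the other hand carry no information about the assigned treatment, so the arms look more alike than the study hands are. The second is bias: the article lists non-blinding of participants and treating surgeons as a limitation, so care of the other hand could come to depend on the allocation. The blinded outcome assessor does not remove this, because the global rating is the participant's own.

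If the BCTQ-SSS were also answered for both hands together, the same mechanism would reach the primary outcome.

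**Working it through.** No figure in the plan bears on this point, so there is nothing to reproduce. The check is to follow the stated rules through for a bilateral participant, and then to see what a size would require.

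**Following the rules.** Success is the global rating at a visit; recurrence is success at 6 weeks and failure later.

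| Study hand | Other hand | Possible rating of overall condition | Consequence |
|---|---|---|---|
| Much better at 6 weeks | Still troublesome | Below the top two categories | Counted as failure although the treated wrist responded |
| Unchanged at 6 weeks | Much better under routine care | One of the top two categories | Counted as success although the treated wrist did not respond |
| Better at 6 weeks and stays so | Worsens later | Success, then failure | Counted as recurrence although the treated wrist did not relapse |
| Better at 6 weeks, relapses later | Troublesome at 6 weeks | Failure at 6 weeks | Cannot count as recurrence |

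Each row follows from the definitions as written. How often each occurs is unknown.

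The study hand is by rule the one with the worse symptoms at baseline. If it improves, the other may become the more troublesome hand and limit how good the overall rating can be. That limit would bind most in the most effective arm.

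**What a size would require.** Let

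- s = success rate if judged on the study hand, with D its difference between two arms;
- b = share of bilateral participants, equal in expectation across arms;
- f = fraction of bilateral participants whose rating is decided by the other hand, taken as equal across arms;
- q = success rate among those ratings, written q1 and q0 for the two arms.

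Taking s as the same in unilateral and bilateral participants, the rated success in one arm is

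(1 − b)·s + b·[(1 − f)·s + f·q] = s·(1 − b·f) + b·f·q,

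and the rated difference is

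D·(1 − b·f) + b·f·(q1 − q0).

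If the other hand fares alike in both arms, q1 = q0 and only the dilution factor (1 − b·f) remains. If its care follows allocation, the second term is a bias of either sign. The article gives none of b, f, q1 or q0, so neither term can be given a value.

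**The primary outcome.** The same reasoning applies to the BCTQ-SSS only if bilateral participants answer for both hands. The Primary outcome measure section neither says so nor excludes it.

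**The other questionnaires.** As described, the sleep questionnaire, EQ-5D, HADS and WLQ-25 concern the person and cannot sensibly be split by hand. They carry the same mixing in bilateral participants, but by their nature and not through a faulty definition.

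**The case against.** The strongest reply concerns the primary outcome. A reader might infer that routine care of the other hand enters the BCTQ-SSS. The documents do not support that: the article is silent on the hand, a study hand is designated, and the instruction could well stand on the case report form, which the quality assurance section says will be developed and which is not shown. This reply stands. For the primary outcome there is a question to confirm, not an error.

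A reader might also want to express the problem as lost power for the primary comparison. That would need a bilateral share and a weight for the other hand in the answer, neither of which is stated. It would also presume that the other hand is rated at all. No such figure is given here.

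The bias argument has limits. The primary contrast is night splint against night splint plus ultrasound. A habit of splinting both hands of anyone given a splint would be common to those two arms and would not separate them; it could matter only against the ultrasound-alone arm. The article states the routine-care rule without reference to arm, so care that follows allocation is a possibility in an unblinded trial and not something that the text describes.

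Finally, the stated aim is the effectiveness of therapeutic ultrasound in patients with carpal tunnel syndrome, and person-level outcomes are a legitimate choice. This stands for the quality-of-life, mood, sleep and work scales. It is weaker for success and recurrence, which are meant to describe the response to the assigned treatment and its durability, and that treatment goes to one hand.

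**Conclusion.** The point holds for treatment success and recurrence. Their stated definition lets a hand outside the randomised comparison decide the outcome in bilateral participants. The expected consequence is dilution if the other hand fares alike across arms; bias is possible if its care differs by arm. For the BCTQ-SSS the article leaves the rated hand open, so the primary outcome may be affected, and no more than that can be said.

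The size and direction cannot be derived, because the bilateral share and the content of routine care are not given. With few bilateral participants the effect would be small. The outcomes known to be affected are secondary and the remedy is cheap, so this is a worthwhile clarification and not a threat to the trial's main conclusion as documented.

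**What to change.** 1. Word the Global Rating of Change for the designated study hand, in place of overall condition, so that success and recurrence both refer to it.
2. Confirm in the protocol that both BCTQ scales are answered for the study hand at every visit, with the hand printed on the form. If the form already does this, one sentence is enough.
3. Record at each visit any treatment given to the non-study hand, and state that this is separate from the diary of off-protocol treatment.
4. Add a supportive analysis in unilateral participants, using the bilateral status already collected at baseline. This also serves the person-level scales, which cannot be split by hand.

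The cost is a changed question stem, a header line, a short log and one extra analysis, with no additional visits or participants. There are two drawbacks: some bilateral participants may find it hard to separate their hands, mainly on the functional items, and the unilateral analysis will be less precise because it uses fewer participants. Nothing here alters how either hand is treated.
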